## Abstract

Although mesenchymal stem cells (MSCs) insertion has gained recent attention as a joint-preserving procedure, no study has conducted direct intralesional implantation of human umbilical cord-derived MSCs (hUCMSCs) in patients with ONFH. This is a protocol for a phase 1 clinical trial designed to assess the safety and exploratory efficacy of human umbilical cord-derived osteoblasts (hUC-Os), osteogenic differentiation-induced cells from hUCMSCs, in patients with early-stage ONFH. Nine patients with Association Research Circulation Osseous (ARCO) stage 1 or 2 will be assigned to a low-dose (1 × 10^7^ hUC-O cells, *n* = 3), medium-dose (2 × 10^7^ cells, *n* = 3), and high-dose group (4 × 10^7^ cells, *n* = 3) in the order of their arrival at the facility, and, depending on the occurrence of dose-limiting toxicity, up to 18 patients can be enrolled by applying the 3 + 3 escalation method. We will perform hUC-O (CF-M801) transplantation combined with core decompression and follow-up for 12 weeks according to the study protocol. Safety will be determined through adverse event assessment, laboratory tests including a panel reactive antibody test, vital sign assessment, physical examination, and electrocardiogram. Efficacy will be explored through the change in pain visual analog scale, Harris hip score, Western Ontario and McMaster Universities Osteoarthritis Index, ARCO stage, and also size and location of necrotic lesion according to Japanese Investigation Committee classification before and after the procedure. Joint preservation is important, particularly in younger, active patients with ONFH. Confirmation of the safety and efficacy of hUC-Os will lead to a further strategy to preserve joints for those suffering from ONFH and improve our current knowledge of cell therapy.

## 1. Introduction

Osteonecrosis of the femoral head (ONFH) usually affects young adults in their 30s to 50s and progresses to femoral head collapse in 60% of asymptomatic patients [1,2]. Total hip arthroplasty (THA) is an effective treatment for advanced ONFH with femoral head collapse but can cause complications such as infection and periprosthetic fracture and may require later revisions due to osteolysis or loosening [3,4,5]. Therefore, joint-preserving procedures must be considered, particularly in the treatment of early-stage ONFH before progression to head collapse, since ONFH often occurs in active, younger patients.

Core decompression is a joint-preserving procedure that can be performed for early-stage ONFH. It has been reported to reduce pressure within the femoral head and promote revascularization to induce bone formation and remodeling [6]. However, a previous study reported that 38% of patients with early-stage ONFH underwent THA at an average of 26 months after core decompression [7], and there has been a controversy regarding the effect of core decompression on early-stage ONFH in previous studies [8,9].

Mesenchymal stem cells (MSCs) insertion, which was used as an adjunctive technique to core decompression, has recently gained attention as a joint-preserving procedure for early-stage ONFH [10,11,12]. MSCs may cause an increase of local cell populations and promote vascular repair and angiogenesis, thereby effectively promoting osteogenesis in the femoral head [13,14]. Several studies have reported that combined core decompression with MSC transplantation in patients with early ONFH showed more satisfactory clinical outcomes and survival rates than core decompression alone [11,12,15]. However, bone marrow or adipocyte-derived MSCs have very diverse cell sourcing and processing strategies, and progenitor cells involved in angiogenesis or bone formation may be insufficient [16]. In comparison, human umbilical cord-derived MSCs (hUCMSCs) have been reported to have osteogenic potential similar to bone marrow- or adipose-derived MSCs and secrete larger amounts of transforming growth factor beta (TGF-β) and vascular endothelial growth factors (VEGFs) [17,18,19]. To date, no study has been conducted to evaluate the safety and efficacy of direct intralesional implantation of human umbilical cord-derived osteoblasts (hUC-Os), osteogenic differentiation-induced cells from hUCMSCs, as a cell therapy for ONFH. The present phase 1 clinical trial is to assess the safety and efficacy of hUC-O-based cell therapy in patients with early-stage ONFH.

## 2. Methods

### 2.1. Aims of This Study

The purpose of this study is to evaluate the safety and exploratory efficacy of hUC-Os. This is a phase I clinical trial in which safety is the main concern and will be determined through adverse event assessment, laboratory tests, vital sign assessment, a physical examination, and an electrocardiogram (ECG) test. In addition, we aim to assess the exploratory efficacy of hUC-Os by comparing subjective preoperative and postoperative patient-reported outcomes, specifically, the pain visual analog scale (VAS) [20], Harris hip score (HHS) [21], and Western Ontario and McMaster Universities Osteoarthritis Index (WOMAC) [22]. Also, we aim to assess the radiographic results after hUC-O-based cell therapy using simple radiography and magnetic resonance imaging (MRI). The preoperative and postoperative the Association Research Circulation Osseous (ARCO) stage [23], necrotic lesion size [24,25], and Japanese Investigation Committee (JIC) stage [26] will be compared.

### 2.2. Study Design

The present study is an investigator-sponsored, prospective, single-institution, open-label, phase 1 clinical trial and has been approved by the institutional review board (IRB) of Kyungpook National University Hospital (IRB No. KNUH 2021-07-015) and Korea Food and Drug Administration (No. 10052) on 1 July 2021. The trial was registered at the Korean Clinical Trials Register (KCT0006627) on 30 September 2021.

### 2.3. Study Population

Participants must fulfill all of the following inclusion criteria to qualify for study enrollment: (1) male and female between the age of 19 and 70; (2) radiographically diagnosed with ONFH; (3) ARCO stage 1 or 2 of the classification criteria for ONFH; (4) symptoms persistent after conservative treatment including medication with duration of at least 3 months; and (5) have voluntarily consented to participate in this clinical trial. Exclusion criteria are as follows: (1) a person with femoral head collapse due to rapidly progressing ONFH; (2) clinically significant abnormal values in a screening test (aspartate aminotransferase (AST) or alanine transaminase (ALT) levels are 2.5 times or more of the upper normal limit specified by the clinical laboratory); (3) malignant bone tumor or bone metastasis in the proximal femur; (4) previous history of malignant tumors (but can be included if there was no relapse within 5 years after completing a treatment); (5) diagnosed with inflammatory arthritis around the femoral head; (6) diagnosed with acetabular dysplasia with a lateral center-edge angle <20°; (7) post-traumatic ONFH; (8) systemic or local infectious disease requiring systemic antibiotic treatment; (9) diagnosed with human immunodeficiency virus (HIV), hepatitis infection; (10) requires continuous, systemic, and high-dose corticosteroid therapy (prednisone administration at 7.5 mg/day or more) or administration of immunosuppressant within 6 months after core decompression; (11) stem-cell therapy for ONFH before screening; (12) heavy alcoholism and overconsumption within 6 months of screening; (13) have undergone core decompression or other treatments or procedures that can affect the femoral head; (14) body mass index ≥ 40 kg/m^2^ at the screening visit; (15) females with a possibility of pregnancy and do not agree to use medically approved contraceptive methods during the study period; (16) pregnant or breastfeeding; (17) received an investigational new drug from another clinical trial within 4 months before participating in this study; and (18) when the investigator determines that the subject is not suitable to participate in this clinical trial.

Of the patients who consent to participate in this clinical trial, those who satisfy the inclusion and exclusion criteria will be assigned to a low-dose (*n* = 3), middle-dose (*n* = 3), and high-dose group (*n* = 3) in the order of their arrival at the facility without random allocation and followed up for 12 weeks. Nine patients will be assigned if no dose-limiting toxicity (DLT) develops up to the highest dose. Depending on the occurrence of DLT, up to 18 patients can be enrolled by applying the 3 + 3 escalation method.

### 2.4. Characteristics and Preparation of the hUC-Os (CF-M801)

The bone-targeted cell therapy, named CF-M801 by developer (CEFO Co., Seoul, South Korea), was produced by inducing osteogenic differentiation of hUCMSCs into hUC-Os using an approved manufacturing method in a factory approved by regulatory agencies. CF-M801 has multiple functions in bone regeneration and angiogenesis and is characterized by the expression of cluster of differentiation (CD) markers [27,28] (Table 1).

CF-M801 consists of 10 million cells/mL and is supplied in frozen form in accordance with the Investigational Product (IP) management policy. An off-white cell suspension is stored under cryogenic conditions (≤−135 °C) and can be used for 1.6 years from the date of manufacture. Vials are transported in a portable freezer prior to use, thawed for 3 to 5 min at 35–37 °C, and must be used within 2 h after thawing. A syringe is filled with the whole volume of cell suspension, shaken to achieve an even cell suspension before administration. A vial has a volume of 1 mL and contains 1 × 10^7^ hUC-Os. In this trial, CF-M801 will be administered into the necrotic lesion of ONFH at a low (1 vial, 1 × 10^7^ cells), middle (2 vials, 2 × 10^7^ cells), or high dose (4 vials, 4 × 10^7^ cells) in the order of group allocation.

### 2.5. Procedure

Core decompression restores normal blood circulation within the femoral head by drilling a tunnel at the site of necrosis [6]. It reduces the increased intramedullary pressure and pain by promoting revascularization within the necrotic site [9]. In this clinical trial, a competent researcher or a designated physician will perform core decompression and administer CF-M801 through the following steps.

First, the size and location of the lesion will be checked before the procedure, and the patient will be placed on the fracture table. Then, a lateral small incision will be made, and a guide pin will be inserted for a core tract under fluoroscopic guidance (Figure 1). Next, an entry hole will be created using a cannulated solid reamer along the pin to guide a following hollow reamer, and an autogenous bone chip (which will be inserted distal to a mixture of hUC-Os) will be collected (Figure 2). Then, a core tract will be created using a hollow biopsy cannula with a diameter of 8–10 mm along the entry hole reaching to necrotic lesion, and a cylindrical autogenous bone block (which will be inserted as a bone plug following inserting autogenous bone chip) will be collected (Figure 3). Curettage will be performed to remove the necrotic bone, and the necrotic bone debris will be washed (Figure 4). During preparation of the recipient site, CF-M801 will be attached with collagen putty using fibrin glue. Collagen putty contains hydroxyapatite (HA) and tri-calcium phosphate (TCP) and can be identified under the fluoroscopic guidance. After the mixture of cell and collagen putty is brought to the necrotic lesion carefully under the fluoroscopic guidance, the remaining space in the core tract will be filled distally with the autogenous bone chip and cylindrical bone block collected in the previous steps. If there is significant space remaining in the distal portion of the core tract, a cylindrical HA and TCP block may be inserted (Figure 5). Gradual partial weight-bearing will be started at 6 weeks, and full weight-bearing walking will be permitted at 3 months postoperatively.

### 2.6. Timeline and Study Protocol

After a volunteer provides written consent to participate in the clinical trial, necessary examinations and tests will be performed within 3 weeks before CF-M801 administration (Visit 1) according to the study protocol (Table 2). Participants who meet the inclusion/exclusion criteria in the eligibility assessment will be subjected to core decompression and CF-M801 administration (Visit 2). Participants will be checked for acute adverse events for 3 days after administration of CF-M801 and will visit the facility after 2 (Visit 3), 6 (Visit 4), and 12 (Visit 5) weeks for a safety assessment. The safety assessment will be performed based on the same schedule for all participants, with only the administration dose varying.

To determine the maximal tolerated dose (MTD) of CF-M801, three participants will be sequentially allocated to a group starting with the low-dose group (1 × 10^7^ cells) according to the standard 3 + 3 dose escalation scheme [29]. The first participants in each dose group will be monitored for acute adverse events including DLT for 3 days after CF-M801 administration. DLT refers to when adverse events related to CF-M801 with grade ≥3 are observed based on the definition from the National Cancer Institute—Common Toxicity Criteria (NCI-CTC) version 5.0 [30]. Another two participants will be assigned to the group when DLT does not occur. Up to 18 patients can be enrolled, depending on the development of DLT. The decision process is as follows: (1) If none of the three participants experiences DLT, the dose will be increased to the next level. (2) If one of the three participants experiences DLT, three participants will be additionally assigned to the same dose group. (3) If one of the six participants (initial three + additional three participants) experience DLT, the dose will be increased to the next level. (4) However, if at least two of the six participants experience DLT, dose escalation will be canceled, and the MTD will become the previous dose level. (5) If at least two of the three participants experience DLT, dose escalation will be canceled, and the MTD will become the previous dose level. (6) If one of the three additional participants show DLT, no additional participants will be assigned to the dose group, and current participants will be monitored for safety.

Participants who will not complete the DLT assessment due to reasons independent of DLT will be deemed an inadequate basis for making decisions regarding dose escalation and an MTD assessment and can be replaced by participants who will be added to the same dose group.

### 2.7. Safety Assessment

Clinically significant abnormal findings from screening or before CF-M801 administration (during a screening test) will be recorded as medical history, and those that satisfy the definition of adverse events following CF-M801 administration will be recorded as adverse events. The safety assessment will be performed in accordance with the study protocol.

#### 2.7.1. Adverse Event

Participants will be instructed to report any adverse events, and researchers will examine participants for adverse events through regular or additional visits, interviews, and their history. DLT will be included as an adverse event. Any adverse events observed will be reported to the IRB throughout the study period.

#### 2.7.2. Laboratory Tests

Laboratory tests will be performed for all participants according to the clinical trial schedule to assess the overall health condition of participants. Participants will be instructed to fast (not allowed to drink beverages except for water or eat food within 8 h before the test) before visiting the facility for blood collection in preparation for laboratory tests. For screening tests (Visit 1), test results obtained in the last 4 weeks may be used instead. One retest may be performed at the discretion of the researcher during the screening period. If a retest has been performed, the results of the retest will be used to determine whether the participant meets the final inclusion and exclusion criteria. The following parameters will be assessed during the laboratory tests.

(1)Blood test: red blood cell (RBC) count, hemoglobin, hematocrit, platelet count, white blood cell (WBC) count, WBC differential count (neutrophil, lymphocyte, monocyte, eosinophil, and basophil), and erythrocyte sedimentation rate.(2)Blood chemistry test: total protein, albumin, total bilirubin, AST, ALT, gamma-glutamyl transpeptidase, blood urea nitrogen, creatinine, glucose, alkaline phosphatase, total cholesterol, triglyceride, uric acid, C-reactive protein, panel reactive antibody (PRA), virus infection test (HIV antigen/antibody, hepatitis B surface antibody, anti-hepatitis C virus antibody, venereal disease research laboratory (VDRL).(3)Urinalysis: protein (albumin), glucose, ketones, WBC, RBC.

Among the blood chemistry tests for viral infections, HIV antigen/antibody, hepatitis B antibody, anti-hepatitis C antibody, and VDRL tests will be performed at Visit 1. Allogeneic immune reaction will be validated through panel reactive antibody (PRA) test at Visit 1 and Visit 5 (Week 12).

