ECG, electrocardiogram; MRI, magnetic resonance imaging; ARCO, Association Research Circulation Osseous; JIC, Japanese Investigation Committee; hUC-Os, human umbilical cord-derived osteoblasts; VAS, visual analog scale; HHS, Harris hip score; WOMAC, Western Ontario and McMaster Universities. ^(a)^ Written consent can be obtained from participants before the screening visit. ^(b)^ For vital signs, pulse, blood pressure, and body temperature will be measured. At Visit 2, vital signs will be measured before hUC-O administration. ^(c)^ For screening tests, test results obtained within 4 weeks after a visit can be used. A retest may also be performed once at the discretion of a researcher during the screening period. The following parameters are assessed during the laboratory tests. Blood test: red blood cell (RBC) count, hemoglobin, hematocrit, platelet count, white blood cell (WBC) count, WBC differential count (neutrophil, lymphocyte, monocyte, eosinophil, and basophil), and erythrocyte sedimentation rate; Blood chemistry test: total protein, albumin, total bilirubin, aspartate aminotransferase or alanine transaminase, gamma-glutamyl transpeptidase, blood urea nitrogen, creatinine, glucose, alkaline phosphatase, total cholesterol, triglyceride, uric acid, C-reactive protein, panel reactive antibody ^(C−1)^, virus infection test (human immunodeficiency virus antigen/antibody, hepatitis B surface antibody, anti-hepatitis C virus antibody, venereal disease research laboratory) ^(C−2)^; Urinalysis: protein (albumin), glucose, ketones, WBC, RBC. ^(d)^ A serum or urine human chorionic gonadotropin test will be performed for women of childbearing age except for those who have been sterilized or are menopausal. Women of childbearing age refer to women who have had their first period, have not been successfully surgically sterilized (via hysterectomy, bilateral tubal ligation, or bilateral oophorectomy), and are not menopausal. Menopause is defined as not having a period for >12 months after the final menstrual period. ^(e)^ Test results obtained within 4 weeks after screening can be used. ^(f)^ Acute adverse events that occur within 3 days after hUC-O administration will be investigated. ^(g)^ Patients will be hospitalized starting 1 day before hUC-O administration and will be monitored throughout the hospitalization period for adverse events. ^(h)^ Performed within 3 days and restrict intake of analgesics within 1 day before hUC-O administration. ^(i)^ For participants who were withdrawn following the group allocation, the procedures scheduled for the last visit will be performed.

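### The only hepatitis B screening test listed is surface antibody, so exclusion 9 has no laboratory check for undiagnosed current hepatitis B

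*Protocol article*

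**What the plan says.** Exclusion 9 in section 2.3 of the protocol article bars anyone "diagnosed with human immunodeficiency virus (HIV), hepatitis infection". It does not name the hepatitis virus, the marker or the result that excludes.

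Section 2.7.2 lists the screening panel as "virus infection test (HIV antigen/antibody, hepatitis B surface antibody, anti-hepatitis C virus antibody", followed by syphilis serology. Later in the same section the timing is given: "HIV antigen/antibody, hepatitis B antibody, anti-hepatitis C antibody, and VDRL tests will be performed at Visit 1". Table 2 footnote (c), under the mark that ties these tests to the screening visit, repeats "hepatitis B surface antibody, anti-hepatitis C virus antibody".

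Screening laboratory results feed into eligibility. If a test is repeated, section 2.7.2 says that "the results of the retest will be used to determine whether the participant meets the final inclusion and exclusion criteria".

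A separate criterion (exclusion 2) covers liver enzymes: "aspartate aminotransferase (AST) or alanine transaminase (ALT) levels are 2.5 times or more of the upper normal limit".

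**The concern.** The panel is labelled as a test for viral infection and is the only laboratory work listed that bears directly on exclusion 9. Its hepatitis B component does not measure infection. Surface antibody is what one expects after vaccination or recovery, and a carrier typically lacks it. A negative result does not clear a candidate, and a positive result does not show infection.

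Two things are at stake. The first is the participant: someone with unrecognised hepatitis B could receive an allogeneic cell product in a trial that meant to keep such people out. The second is interpretation. AST, ALT and bilirubin are among the safety laboratory tests. In an undetected carrier, a rise during follow-up could come from the hepatitis or from CF-M801, and the data as collected would not separate the two.

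**Working it through.** No arithmetic applies. The check is to compare every mention of the hepatitis B test with the criterion it should serve, and then to look for any other route that closes the gap.

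**1. Which marker is named?**

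| Place | Hepatitis B marker |
|---|---|
| Section 2.7.2, blood chemistry list | surface antibody |
| Section 2.7.2, sentence on Visit 1 timing | antibody, type not given |
| Table 2, footnote (c) | surface antibody |

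Three of three mentions name an antibody. Surface antigen, core antibody and viral DNA appear nowhere, so the text never corrects itself.

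**2. Does the marker fit its label?** The neighbouring entries do. HIV is tested by antigen/antibody and hepatitis C by anti-HCV antibody, and both are suited to infection screening. Only the hepatitis B entry is a marker of immunity or past infection.

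**3. What else could keep a carrier out?**

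- *Known diagnosis.* Exclusion 9 is worded in terms of a diagnosis, and Table 2 schedules a medical history review at Visits 1 and 2. This removes candidates who know they are infected.
- *Liver enzymes.* Exclusion 2 removes candidates with AST or ALT at 2.5 times the upper limit of normal or more. This catches some active disease, but not a carrier with normal or mildly raised enzymes.
- *Investigator judgement.* Exclusion 18 is open-ended, but it can act only on what the investigator knows.

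What remains is current hepatitis B that is undiagnosed and has AST and ALT below the limit.

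**4. Would follow-up reveal it?** Table 2 marks the viral panel for Visit 1 only. Routine laboratory tests recur at Visits 3, 4 and 5 (Weeks 2, 6 and 12), so an enzyme rise could be seen, but no scheduled test would identify hepatitis B as its cause.

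**5. Is this only detail left out of a condensed article?** No. The article names a specific assay and gives it a purpose it cannot serve. That is a statement to correct, not a missing detail.

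**The case against.** The strongest reply is that the gap is narrow, and this stands. A reader might infer that the whole hepatitis exclusion goes unenforced. The document does not support that: a known diagnosis excludes without any assay, hepatitis C has its own test, and the enzyme limit removes some active disease.

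A reader might also infer that immune or vaccinated candidates are turned away, which would slow recruitment. Calling the assay an infection test invites that misreading, but no sentence says that a positive surface antibody excludes anyone, and no accrual figure is given.

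It is tempting as well to carry the point through to dose escalation, since one dose-limiting toxicity (DLT) among three participants changes the next step. The document does not show that route. Under section 2.6 a DLT must be grade 3 or higher and related to CF-M801. The only stated watch for it is 3 days, given for the first participant in each group, and Table 2 has no scheduled laboratory test after dosing until Week 2. No window is stated for the other participants, so the route cannot be ruled out, but nothing establishes it.

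Nor can the risk be sized by assuming a carrier prevalence and computing the chance of at least one carrier among 9 or 18 participants. That counts diagnosed carriers too and says nothing about whether a severe rise follows or how it is attributed. The document supplies none of these quantities.

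Finally, antibody may be a writing or translation slip for antigen, with the correct assay actually run. That is possible, and the article cannot settle it. If so, the remedy is a text correction, but the wording would still be wrong in all three places.

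**Conclusion.** The point holds in a limited form. As written, screening has no laboratory check for undiagnosed current hepatitis B in candidates whose AST and ALT are below the exclusion limit, and the document does not say which result counts as hepatitis infection. The consequences are exposure of a participant whom the criterion was meant to keep out, and a competing explanation for later liver-enzyme rises in a study whose main concern is safety.

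The size cannot be given in numbers from the document. Nothing here alters the sample size or the 3 + 3 rules.

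The conclusion rests on two assumptions: that the article's wording reflects the assay actually ordered, and the general meaning of surface antibody as a marker of immunity or past infection, which the document itself does not discuss.

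**What to change.** Reconcile the marker in section 2.7.2 (both mentions) and Table 2 footnote (c) with exclusion 9.

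- If surface antibody is what is ordered, list a marker of current infection, hepatitis B surface antigen, at Visit 1. Surface antibody may be kept as information only.
- If antibody is a slip for antigen, check the operative protocol and laboratory order, and correct all three mentions.
- In either case, the sponsor should state which result counts as hepatitis infection under exclusion 9.

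The cost is at most one assay substituted on blood already drawn at screening, plus short text corrections. No visit or design change is needed.
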